Transplant-related BMD loss is a rapidly evolving, and long-lasting disorder. The loss of BMD following aHSCT can be attributable to multiple factors, such as high-dose chemotherapy, the use of immunosuppressive therapy, and decreased activity (3). BMD is significantly lower in pre-aHSCT population than in age-matched general population (4). Further bone loss can occur as early as 100 days post-transplant (5) and progress over for 2-6 years, leading to persistent osteoporosis (6-8) and higher fracture rates (3).

*1.2 Vitamin D Deficiency* *among aHSCT Patients*

Vitamin D, as the precursor to the potent steroid hormone calcitriol, plays an important role in regulation of the systemic calcium, and is essential to preserve bone mass. Vitamin D deficiency can be resulted from the lack of sun exposure, impairment of liver and kidney function, and chronic use of corticosteroids (9-11). Vitamin D deficiency may also play a role in bone loss, but has not been carefully studied to date in the aHSCT population.

Osteoporosis, caused by a loss of bone tissue, can be measured by dual energy X ray absorptiometry *(*DXA), which is one of the most accurate and precise methods for measuring bone mineral density and determine the risk for fractures.

In a review of 265 patients undergoing aHSCT at the Leukemia/BMT Program of British Columbia during Jan, 2012 to July, 2016, we found that 62% patients were vitamin D insufficient or deficient at the baseline (pre-aHSCT) (Figure1). It has been reported by others that 60-70% aHSCT survivors have vitamin D deficiency (8,11). Vitamin D supplementation has been strongly recommended for aHSCT patients (12-14); however, 47% of patients failed to achieve sufficient 25-OH-D3 levels by 100 days post-aHSCT by taking recommended regimen, 2000 IU vitamin D3 daily (Figure 2).

*1.3 Vitamin D and Immunomodulatory Function*

Immunomodulatory actions of vitamin D have been recognized for over a few decades (15,16), but it is only in the last few years that the significance of this to normal human physiology. It has become apparent after a number of observations have suggested that vitamin D is a key factor linking innate and adaptive immunity, and both of these functions may be compromised under conditions of vitamin D insufficiency (17-20).

Vitamin D binds and activates vitamin D receptor, which is expressed in several cell types in the immune system, including in T lymphocytes and antigen presenting cells, such as dendritic cells (10;11). Vitamin D has been implicated in promoting the production and function of T regulatory cells which are critical mediators of immune system (10). Vitamin D can also act directly on T lymphocytes to inhibit their proliferation (12).  Studies have shown that vitamin D supplementation promotes better immune function in the reconstituted immune system (21, 22).

**2. STUDY RATIONALE**

Sustained optimal vitamin D level is essential in preventing bone loss after aHSCT. However, studies from us (Figure 2) as well as others have shown that an optimal 25-OH-D3 level is difficult to achieve in aHSCT recipients by a vitamin D3 regimen recommending 2000 IU vitamin D3 daily (23).

Studies have demonstrated that an oral loading dose of 100,000 IU vitamin D3 is safe and helpful in maintaining an adequate 25-OH-D3 level in people with various medical conditions, including patients who were critically ill (24-26).

Significant bone loss initiates before aHSCT and progresses rapidly at the early stage of post-aHSCT, therefore, prophylactic interventions can be essential to prevent severe bone loss and osteoporosis in long-term survivors of aHSCT. We propose a clinical trial randomizing patients to standard of care which is vitamin D3 2000 IU per day versus 100,000 IU vitamin D loading dose with 2000 IU per day.

The primary endpoint would be to achieve and maintain sufficient 25-OH-D3 levels (>75 nmol/L) in patients 100 days after undergoing aHSCT at the Leukemia/BMT Program of British Columbia.

**3. OBJECTIVES**

*3.1 Primary Objective*

To assess the efficacy (the proportion of patients achieving sufficient serum 25-OH-D3 level) after a single oral loading dose of 100,000 IU vitamin D3 prior to aHSCT, with subsequent vitamin D3 2000 IU daily, in preventing vitamin D insufficiency/deficiency in the first 100 days post-aHSCT.

*3.2 Secondary Objective*

To compare the effect of a single oral 100,000 IU vitamin D3 loading dose with our standard of care (2000 IU vitamin D3 daily) in terms of

1. BMD of spine and hip, trabecular bone score (TBS) at three months and one year post aHSCT.

2. Immunological and inflammatory biomarkers.

**4. STUDY DESIGN**

*4.1 Study Randomization*

This study will randomize patients 1:1 using block randomization.

*4.2 Arm A (Control Group)*

Participants assigned to the control group will be advised to take our current vitamin D regimen (2000 IU vitamin D3 daily).

*4.3 Arm B (Intervention Group)*

Participants assigned to the intervention group will receive a single oral loading dose of 100,000 IU vitamin D3 on the second day of hospital admission for aHSCT, then 2000 IU vitamin D3 daily.

The vitamin D3 2000 IU daily supplement will be provided on discharge for all study participants.

*4.4 Data Collection and Endpoints*

Serum 25-OH-D3 levels will be measured at baseline (pre-aHSCT), 30 and 100 days post-aHSCT. As vitamin D is involved in the regulation of serum phosphate and calcium, we will also measure serum calcium, phosphate, ALP, and PTH at these time points. To monitor bone health, bone mineral density (BMD) will be assessed by dual-energy x-ray absorptiometry (DXA) at baseline, 100 days and one year post-aHSCT as standard of care.

*4.5 Baseline Demographics*

Demographic data will be collected by patient interviews at baseline, including age, other health conditions, fracture risk factors, calcium and vitamin D intake. Medical and transplantation variables will be obtained from patients' medical records.

# 5. Eligibility and Study Entry Criteria

Eligible patients will be identified by chart review prior to the transplant. Inclusion and exclusion criteria must be met as outlined in Sections 5.1 and 5.2 before the patients are randomized. Randomization will be done on the day of admission for aHSCT at the Leukemia/BMT Program of British Columbia.

##### 5.1 Inclusion Criteria

1. Patients undergoing allogeneic stem cell transplantation at the Leukemia/BMT Program of British Columbia.
2. Age greater than or equal to 18 years.
3. Able to provide written informed consent.

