##### 8.2 Determination of Sample Size

Sample size is derived from the primary objective, based on results of our previous study showing that the average serum 25-OH-D3 levels were 50nmol/L at baseline and increased to 72 nmol/L at 100 days post-HSCT. The standard deviation of the mean change in 25-OH-D3 from baseline to 100 days post-aHSCT was 18.6 among 89 patients (61%) who had vitamin D3 insufficiency. In order to detect a 25% additive increase (from 61% to 86%) in the proportion of patients achieving sufficient serum 25-OH-D3 level (>75nmol/L) at day 100 post-aHSCT, we need 38 subjects in each group. We would therefore be able to reject the null hypothesis that the mean change in 25-OH-D3 levels between the intervention and control groups is equal with 80% power and a type I error of 5%, using one-sided t-test. To account for a maximum 10% transplant-related mortality at day100 post-transplant, we plan to enroll 84 patients (42 in each group).

*8.3 Analyses Supporting the Primary Objective*

The primary objective is to assess effect of a single oral loading dose of 100,000 IU vitamin D3 followed by 2000 IU vitamin D3 daily in preventing vitamin D insufficiency in aHSCT recipients, compared to 2000 IU vitamin D3 daily as the standard regimen.

Subjects who die between the time of randomization and day 100 will not be included in the analysis.

The primary analysis will be unadjusted and consist of a 2-sample, 1-sided, 0.05-level, t-test comparing the proportion of patients achieving normal serum 25-OH-D3 from baseline to 100 days post-aHSCT in control and intervention groups. To corroborate this analysis, a multivariable Gaussian regression model will be fit to include adjustment by age, sex, and disease (acute leukemia vs others).

The analysis described above will be corroborated by a per-protocol analysis to include only those subjects who provided both a baseline and 100 post-transplant serum 25-OH-D3.

*8.4 Analyses Supporting Secondary Objectives*

Analyses similar to those described for the primary objective will be performed.

#

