# Figure 2. Optimal vitamin D levels (>75nmol/L) were not achieved by standard vitamin regimen (2000 IU vitamin D3 daily) at 100 days post-transplant for patients with pre-transplant vitamin D insufficiency or deficiency (<75nmol/L).

#

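### Section 8.2 assumes a uniform rise from 61% to 86% without saying whom the 61% describes; about 38% are expected to enter already sufficient, so the overall gain may be diluted and the 80% power is unsupported for the enrolled mix

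*Protocol*

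**What the plan says.** - **Eligibility.** Protocol section 5.1 takes adults who can consent and describes the population as "Patients undergoing allogeneic stem cell transplantation at the Leukemia/BMT Program of British Columbia". Neither this list nor the exclusion criteria set a baseline 25-OH-D3 limit.
- **Expected mix.** Section 1.2 reports, from 265 transplant patients, that "62% patients were vitamin D insufficient or deficient at the baseline". Figure 1 shows 38.11% (101), the complement.
- **Planning data.** Section 8.2 gives an SD of change that "was 18.6 among 89 patients (61%) who had vitamin D3 insufficiency". The Figure 2 caption limits the day-100 result on the standard regimen to a similar group: "for patients with pre-transplant vitamin D insufficiency or deficiency (<75nmol/L". Section 1.2 cites that figure for a 47% failure rate, which is 53% success.
- **Sample size.** Section 8.2 continues: "In order to detect a 25% additive increase (from 61% to 86"%), "we need 38 subjects in each group", "with 80% power and a type I error of 5%, using one-sided t-test".
- **Analysis.** Sections 4.1 and 8.1 describe 1:1 block randomisation and name no strata. Section 8.3 makes the primary comparison unadjusted. Its supporting model adjusts for age, sex and disease, but not for baseline 25-OH-D3.

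**The concern.** Two things are left open in section 8.2.

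First, the 61% has two meanings within a few lines. It is the proportion who were insufficient ("18.6 among 89 patients (61%) who had vitamin D3 insufficiency") and then the proportion in the control arm who are sufficient at day 100. It matches neither the 53% success rate in insufficient patients nor any stated all-comer rate.

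Second, every planning figure whose population is stated comes from patients insufficient before transplant, while the trial will enrol a mix. For someone already above the cut-off, success at day 100 means staying there, and the loading dose may add less. The difference that the trial estimates is a weighted average over both groups. If the second group gains less than 25 points and the first gains 25, the overall gain falls short of 25. The trial could then miss an effect that is fully present in the insufficient patients.

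**Working it through.** **Inputs.** From section 8.2: 61% vs 86%, one-sided 5%, 38 evaluable per arm. From section 1.2 and Figure 1: 62% insufficient, so 38% sufficient. From section 1.2 with the Figure 2 caption: 53% control success in the insufficient. Assumed, because the documents do not give them: q, the control day-100 rate in baseline-sufficient patients, and g, their gain.

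**Step 1: the plan's own figure.** Pooled two-proportion formula, p̄ = 0.735:

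n = [1.645·√(2·0.735·0.265) + 0.842·√(0.61·0.39 + 0.86·0.14)]² / 0.25² = 37.5, so 38 per arm.

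Power at 38 = Φ[(d − 1.645·SE0)/SE1] = Φ[(0.25 − 1.645·0.1013)/0.0971] = 80.5%. Here SE0 is the pooled and SE1 the unpooled standard error. The stated N reproduces from the two proportions alone; the SD of 18.6 is not needed.

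**Step 2: the mixture.** With control rate c in the insufficient and a 25-point gain there:

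- control = 0.62·c + 0.38·q
- intervention = 0.62·(c + 0.25) + 0.38·(q + g)
- overall gain = 0.62·25 + 0.38·g points (g in points), which is 15.5 when g = 0.

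Example, c = 0.53, q = 0.80, g = 0: control 0.3286 + 0.3040 = 0.633; intervention 0.4836 + 0.3040 = 0.788. Power = Φ[(0.155 − 1.645·0.1041)/0.1026] = 44%.

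**Step 3: the range.** Both starting rates are shown because the meaning of 61% is unsettled. The range of q is cut where q + g would pass 100%.

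| Gain g in the sufficient | q | Overall gain (points) | Power, c = 53% | Power, c = 61% |
|---|---|---|---|---|
| 0 | 70-100% | 15.5 | 42-50% | 44-57% |
| 10 | 70-90% | 19.3 | 57-64% | 61-71% |
| 20 | 70-80% | 23.1 | 72-76% | 77-82% |
| 25 | 70-75% | 25.0 | 79-81% | 84-86% |

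With g = 0, 80% power would need 86-113 evaluable per arm (c = 53%) or 70-103 (c = 61%).

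**Step 4: could 61% already be an all-comer rate?** Solve 0.62·0.53 + 0.38·q = 0.61: q = (0.61 − 0.3286)/0.38 = 0.74. That is a possible value. If the insufficient then rise to 78%, reaching 86% overall needs (0.86 − 0.62·0.78)/0.38 = 0.99 in the sufficient, a rise from 74% to 99%. At q = 0.74, power is 42% with no gain in the sufficient, 58% with 10 points, 74% with 20 and 80% with 25.

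**Step 5: what stratifying buys.** I used an approximate Mantel-Haenszel risk-difference calculation with c = 53% and g = 0. The null and alternative variances are formed within each stratum and weighted 0.62 and 0.38. For q = 70%, 80%, 90% and 100%, power is 42%, 44%, 49% and 57%, against 42%, 44%, 46% and 50% unstratified.

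**The case against.** The strongest reply is that N was never shown to rest on insufficient-only data. It comes from 61% vs 86%, and step 4 shows that 61% can be a rate for everyone enrolled. On that reading the 25 points are an all-comer target, perhaps optimistic, but not a figure borrowed from the wrong group. This stands: a reader might infer that the plan applied an insufficient-only success rate to all-comers, and the documents do not establish that. It does not rescue the 80%, however. With a 25-point gain in the insufficient, the target still needs almost every baseline-sufficient patient to succeed, and nothing in the protocol supports that.

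A second reply is that zero gain in the sufficient is only an assumption. If 30% of them would fall below the cut-off on standard care, they have up to 30 points to gain. This also stands, and it is why the result is a range.

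Third, broad eligibility fits the aim. Section 3.1 speaks of preventing insufficiency, and section 2 of achieving and maintaining sufficient levels. Agreed: the inclusion criterion is not the error; the defect lies in section 8.2.

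Fourth, stratification recovers little power. That is true except when nearly all baseline-sufficient patients stay sufficient.

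**Conclusion.** The point holds in conditional form. Section 8.2 does not identify the population behind its 61%, and it applies one 25-point gain to a mix for which the protocol documents only the insufficient part. If the insufficient gain 25 points and the 38% already sufficient gain nothing, the overall gain is 15.5 points and power at 38 per arm is about 42-57%. With a 10-point gain in the sufficient it is about 57-71%. It is about 80% or more only if their gain matches or comes close to that in the insufficient.

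These figures assume that the trial's mix resembles the 265 reviewed patients, that 53% or 61% is the control rate in the insufficient, and that q is 70-100%. The documents do not support the stronger conclusion that the effect will be diluted or that the trial will probably miss a real one, because they give no day-100 rate or gain for baseline-sufficient patients. It should be fixed, but it does not invalidate the design.

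**What to change.** Keep eligibility and N.

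1. **Section 8.2.** State which population the 61% describes and reconcile it with the 53%. Write the control rate and expected gain separately for patients below and at or above the cut-off. Restate the power for the expected 62/38 mix as a range.
2. **Sections 8.1 and 8.3.** Stratify or adjust the primary comparison of proportions by baseline 25-OH-D3 below versus at or above the cut-off, for example with a Mantel-Haenszel risk difference. Add baseline 25-OH-D3 to the supporting model. Stratify randomisation too where the result is available on the day of admission; otherwise stratify in the analysis only.
3. **Section 8.3.** Report the estimate and confidence interval in the baseline-insufficient stratum as a supportive result, since the planning data describe that group.

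The cost is wording and a two-level factor from a blood test already scheduled at baseline, with no extra visits or patients. The stated power will become less favourable, and these changes do not by themselves bring it back to 80%.

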##### Exclusion Criteria

1. History of kidney stones, hypercalcemia, hypervitaminosis D, or allergic/ sensitive to vitamin D.

2. Not meeting eligibility criteria to proceed with allogeneic stem cell

transplantation as per the Leukemia/BMT Program of BC.

##### 5.3 Informed Consent

The participants must acknowledge in writing their consent to be a study subject.

##### 5.4 Protocol Approval

This protocol must be reviewed and approved by the Research Ethics Board (REB) prior to approaching participants for this study.

# 6. STUDY PROCEDURES

Blood work will be sampled at baseline (pre-aHSCT), post-aHSCT day 30, and day 100. Bone mineral density (BMD) will be assessed by dual-energy x-ray absorptiometry (DXA) at baseline, 100 days and one year post-aHSCT, respectively, as part of standard of care.

*6.1 Informed Consent*

The subject must read, understand, and sign the REB-approved informed consent form (ICF) confirming his or her willingness to participate in this study. In addition, subjects must sign all approved ICF amendments per the REB guidelines during the course of the study.

*6.2 Confirmation of Eligibility*

All necessary procedures and evaluations will be performed to document that the subject meets all eligibility criterion (Section 5).

*6.3 Baseline Demographics*

Demographic data will be collected by patient interviews at baseline, including age, medical history and baseline medications. Medical and transplantation variables will be obtained from patients' medical records.

*6.4 Biochemistry and Bone Mineral Density Analysis*

Serum 25-OH-D3 levels will be measured pre-transplant (baseline), 30 and 100 days post-aHSCT, respectively. Measurements of baseline biochemistry (calcium, phosphate, ALP, PTH) will be conducted at pre-transplant, day 30, 100, and one year post-aHSCT. BMD by DXA scan will be performed at pre-transplant, day100, and one year post-aHSCT, respectively, as part of our routine standard of care.

*6.5 Immune and inflammatory biomarkers*

We will connect this study to Hematology Cell Bank of BC and the Legacy Cell Bank of BC in which blood samples are collected at the time of diagnosis and subsequent follow-up periods. This linkage will allow us to obtain study samples without additional phlebotomy. We will request in writing (email) to the project coordinator to obtain blood samples matching proposed study time points.

Markers of immune function including total white blood cell count, lymphocyte count, CD4+ and CD8+ subsets of T-lymphocytes, and T-regulatory cells will be tested at pre- and day 100 post-transplant. Studies from other (6a) as well as [name] laboratory specialized in T-regulatory cell function in the aHSCT population have demonstrated the role of T-regulatory cells in the pathogenesis of GVHD (27, 28)

# 7. SAFETY PROCEDURE

# We do not anticipate adverse events attributable to this single dose vitamin D3 intervention.

**8. STATISTICAL METHODS**

##### 8.1 Randomization

Subjects will be randomized into either the control group or the intervention group using 1:1 block randomization.

##### 8.2 Determination of Sample Size

Sample size is derived from the primary objective, based on results of our previous study showing that the average serum 25-OH-D3 levels were 50nmol/L at baseline and increased to 72 nmol/L at 100 days post-HSCT. The standard deviation of the mean change in 25-OH-D3 from baseline to 100 days post-aHSCT was 18.6 among 89 patients (61%) who had vitamin D3 insufficiency. In order to detect a 25% additive increase (from 61% to 86%) in the proportion of patients achieving sufficient serum 25-OH-D3 level (>75nmol/L) at day 100 post-aHSCT, we need 38 subjects in each group. We would therefore be able to reject the null hypothesis that the mean change in 25-OH-D3 levels between the intervention and control groups is equal with 80% power and a type I error of 5%, using one-sided t-test. To account for a maximum 10% transplant-related mortality at day100 post-transplant, we plan to enroll 84 patients (42 in each group).

*8.3 Analyses Supporting the Primary Objective*

The primary objective is to assess effect of a single oral loading dose of 100,000 IU vitamin D3 followed by 2000 IU vitamin D3 daily in preventing vitamin D insufficiency in aHSCT recipients, compared to 2000 IU vitamin D3 daily as the standard regimen.

Subjects who die between the time of randomization and day 100 will not be included in the analysis.

The primary analysis will be unadjusted and consist of a 2-sample, 1-sided, 0.05-level, t-test comparing the proportion of patients achieving normal serum 25-OH-D3 from baseline to 100 days post-aHSCT in control and intervention groups. To corroborate this analysis, a multivariable Gaussian regression model will be fit to include adjustment by age, sex, and disease (acute leukemia vs others).

The analysis described above will be corroborated by a per-protocol analysis to include only those subjects who provided both a baseline and 100 post-transplant serum 25-OH-D3.

*8.4 Analyses Supporting Secondary Objectives*

Analyses similar to those described for the primary objective will be performed.

#

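### The adjusted model in 8.3 omits baseline 25-OH-D3: avoidable loss of precision, no bias in the primary test; baseline should also be defined as pre-dose

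*Protocol*

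**What the plan says.** Section 8.3 of the protocol describes the main comparison this way: "The primary analysis will be unadjusted and consist of a 2-sample, 1-sided, 0.05-level, t-test". The supporting analysis is a single regression: "a multivariable Gaussian regression model will be fit to include adjustment by age, sex, and disease (acute leukemia vs others". The covariate list is closed, so this is a choice made in the protocol and not one left open.

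Section 4.4 schedules the outcome variable for all participants: "Serum 25-OH-D3 levels will be measured at baseline (pre-aHSCT), 30 and 100 days post-aHSCT". Section 6.4 repeats the schedule and equates baseline with pre-transplant. Sections 4.1 and 8.1 specify 1:1 block randomisation and name no stratification factor.

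On timing, section 5 places randomisation on the day of admission. Section 4.3 gives Arm B "a single oral loading dose of 100,000 IU vitamin D3 on the second day of hospital admission for aHSCT", and section 3.1 describes that dose as preceding the transplant.

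**The concern.** Being above 75 nmol/L at day 100 should depend on where the patient started, and the protocol's own background treats it so. Section 1.2 reports that 62% of an earlier cohort were insufficient or deficient before transplant, which leaves about 38% already sufficient. The Figure 1 bands run from below 25 to above 74 nmol/L, and Figure 2 is restricted to patients who were low before transplant. Section 5 restricts entry by history of hypervitaminosis D but not by baseline level. The trial will therefore mix patients who need only stay above the threshold with patients who must climb to it.

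An adjusted model meant to corroborate the primary result should account for that spread. Age, sex and disease do so only as far as they happen to correlate with baseline level. What is at stake is precision, and protection of the adjusted estimate against a chance baseline difference.

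The timing wording is a linked but smaller matter. A sample taken after the loading dose but before transplant would meet the written definition of baseline, yet in Arm B only it would already contain treatment effect.

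**Working it through.** **Inputs from section 8.2.** The effect is "a 25% additive increase (from 61% to 86%) in the proportion of patients achieving sufficient serum 25-OH-D3 level". The error rates are "with 80% power and a type I error of 5%, using one-sided t-test". The evaluable number is given as: "we need 38 subjects in each group". The section also gives an SD of change of 18.6 nmol/L, but no correlation between baseline and day 100. That correlation, ρ, is an assumption below and is shown at 0, 0.3, 0.5 and 0.7.

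**1. The plan's own figure.** One-sided two-proportion formula with pooled variance under the null and no continuity correction; mean proportion 0.735; z values 1.645 and 0.842:

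n = [1.645·√(2·0.735·0.265) + 0.842·√(0.61·0.39 + 0.86·0.14)]² / 0.25² = 37.5, so 38 per group.

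The stated 38 reproduces, and power at 38 is 80.5%. This figure is not in dispute.

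**2. Chance imbalance in baseline.** In SD units, the standard error of the baseline difference is √(2/38) = 0.23. The probability of a difference above 0.3 SD in either direction is 2·[1 − Φ(0.3/0.229)] = 19%; above 0.5 SD it is 3%. With all 42 enrolled per arm the values are 17% and 2%.

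To see what such an imbalance does, take a latent normal scale at the 61% rate. A 0.3 SD difference shifts the sufficiency proportion by Φ(Φ⁻¹(0.61) + 0.3ρ) − 0.61, which is 3.4, 5.6 and 7.8 percentage points at ρ = 0.3, 0.5 and 0.7. The design effect is 25 points.

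**3. Continuous scale.** Adjusting for baseline multiplies residual variance by 1 − ρ². For a difference that has 80% power unadjusted, adjusted power is Φ[(1.645 + 0.842)/√(1 − ρ²) − 1.645].

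| ρ (assumed) | Variance factor | Variance removed | Power |
|---|---|---|---|
| 0.3 | 0.91 | 9% | 83% |
| 0.5 | 0.75 | 25% | 89% |
| 0.7 | 0.51 | 49% | 97% |

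**4. Binary endpoint.** Simulation of 100,000 trials per row with 38 per group. A latent normal day-100 value correlates ρ with baseline and is cut to give 61% and 86% sufficient. A linear model for the binary outcome is fitted without and with baseline and tested one-sided at 5%. Type I error is simulated with 61% in both groups.

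| ρ (assumed) | Power, unadjusted | Power, adjusted | Type I error, unadjusted / adjusted |
|---|---|---|---|
| 0 | 81.1% | 80.7% | 4.7% / 5.0% |
| 0.3 | 81.3% | 82.5% | 4.6% / 4.9% |
| 0.5 | 81.3% | 85.5% | 4.6% / 5.0% |
| 0.7 | 81.4% | 90.0% | 4.6% / 5.0% |

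If baseline turned out to carry no information, adding it would cost less than half a percentage point of power.

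**5. Timing.** Set in order, sections 5, 4.3 and 3.1 give randomisation on the admission day, loading dose on the next day, then transplant. Sections 4.4 and 6.4 bound the baseline sample only by the transplant. If a post-dose sample in Arm B were raised by d, a change score would be shifted by −d and a baseline-adjusted estimate by about −β·d, where β is the slope on baseline. Both act against the intervention. A comparison of day-100 proportions uses no baseline value and is unaffected.

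**The case against.** Several points on the other side stand.

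- The regression is corroborative and the primary test is explicitly unadjusted. A reader might infer that omitting baseline biases or invalidates the trial's result. It does not: randomisation protects the comparison, and the error rate of the unadjusted test already allows for chance imbalance.
- A reader might also infer that a sizeable baseline imbalance is likely. A 19% chance of more than 0.3 SD does not support that word.
- The gain depends on a correlation the protocol does not give. At 0.3 it is about one point of power on the binary endpoint. That baseline is the strongest predictor is plausible but not shown.
- Scheduled is not the same as measured. Section 8.3 plans a per-protocol set of subjects with both values, so some baselines may be missing, and a complete-case adjusted model would lose those patients.
- Baseline ordinarily means before treatment, and nothing in the protocol points to a post-dose draw. Inferring that the primary comparison of proportions is at risk from such a draw goes too far, because that comparison does not use baseline.

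One counter-argument is only partly right. Section 8.2 frames the null hypothesis as a mean change, and 8.3 mentions the span from baseline to day 100, so one could say that baseline is already in the primary analysis. The quantity compared in 8.3 is nevertheless a proportion, and baseline is absent from the regression's covariates on either reading. Whether the endpoint is a proportion or a change is a separate question.

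**Conclusion.** The omission is real and is fixed in the protocol text. Its consequence is lost precision and a supportive model that cannot correct chance baseline imbalance; there is no bias in the primary comparison. The size ranges from slight to useful: about 1, 4 and 9 points of binary-endpoint power at correlations of 0.3, 0.5 and 0.7, or 9%, 25% and 49% of residual variance on the continuous scale. These figures rest on the assumed correlations, a latent normal model, the design rates of 61% and 86%, and 38 evaluable patients per group.

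The timing point is a clarification. It matters only for analyses that use baseline (the amended regression or any change score), and it is a condition for using baseline safely as a covariate.

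**What to change.** - **Section 8.3:** add baseline 25-OH-D3, as a continuous variable, to age, sex and disease in the regression. Keep the unadjusted test as primary.
- **Missing baselines:** state a simple rule, for example imputing the overall mean, so that a missing baseline does not remove a patient from the adjusted model.
- **Sections 4.4 and 6.4:** define the baseline value as the last sample drawn before the loading-dose time point (the second day of admission), applied identically in both arms.

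The cost is one covariate and two sentences. No new visit or assay is needed, and neither the sample size nor the treatment schedule changes.
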